## Abstract

Purpose: The purpose of this protocol was to discover the connection between patients with non-surgical pain or other discomfort and their psychosocial status. Cognitive behavior therapy will be used, which we verified will determine the effect and feasibility of postoperative rehabilitation processes. Materials and Methods: This study will include 200 patients ranging from 18 to 60 years old who have underwent or will undergo FAI arthroscopy in the West China Hospital Sports Medicine Center from 2023 to 2026. A standardized prospective single-center parallel-group randomized controlled trial will be used for these participants. The participants will be divided into intervention (telephone versus face-to-face versus music versus floatation) and control groups. The follow-up periods will be measured pre-operatively, as well as postoperatively at 1, 3, and 6 months. The primary outcomes will include the modified Harris Hip Score (mHHS) and the Visual Analogic Score (VAS), and the secondary outcomes will include the range of motion (ROM), the Huaxi Emotional-distress Index (HEI), and the depression, anxiety, and stress scale (DASS-21 scale). Furthermore, the Patient Health Questionnaire-9 (PHQ-9) and a Short-Form 12 (SF-12) questionnaire will also be evaluated. Discussion: This study will evaluate the clinical and cost-effectiveness of different types of psychosocial-therapy-based rehabilitation methods designed to improve the quality of life of FAI patients with persistent symptoms.

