Additionally, patients after total hip or knee arthroplasties with infection suffered from psychological burdens, implying a correlation [9]. Bay et al. performed a systematic psychological evaluation of total hip arthroplasty (THA) patients and found that psychological interventions were not routinely applied for THA; therefore, determining the applicable conditions for and optimal usage of THA is still required [10]. Additionally, there were no comparisons between different psychosocial interventions in FAI patients in the literature.

Therefore, this trial’s primary objective is to compare the effectiveness of different psychosocial therapies for improving the quality of life of FAI participants with persistent postoperative symptoms. The secondary objective is to determine the relationship between clinical effectiveness, patients’ feedback, and relative cost-effectiveness.

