### 4.5. Sample Size

The primary endpoint will be altered from baseline to 6 months post-surgery in the mHHS scale. A pilot trial was conducted, and the baseline suggested the targeted patients’ population, with a mean mHHS of 85.1 and an SD of 8.7. The minimal clinically important difference (MCID) for the mHHS scale in this population is 8 points [29,42]. Therefore, the sample size of this study will be calculated based on the mHHS SD of 8.7 and the MCID of 8.

G*power software (version 3.1.9.7 for Windows XP, Vista, Germany) was used to calculate the sample size, with an effect size of 0.8 and power of 90%, and a sample size of 34 in each group is required for the minimum inclusion. Considering the allowance of 15% for a loss of follow-up for 12 months postoperatively, 40 participants will be recruited in each group.

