### 4.6. Statistical Analysis

Statistical analysis will be conducted through IBM SPSS 22.0. The primary purpose of this protocol is to discover the connection between the relief of pain or discomfort post-operation and the medical staff’s psychological intervention. Primary outcomes will be estimated to determine the statistical significance (at a significance level of 0.05). Other outcomes and different endpoints aiming at illustrating the patient’s psychological conditions and the rehabilitation situations would also be analyzed. Descriptive analysis will be conducted to explore the effects of subgroups based on specific surgical techniques. Analysis of covariation (ANCOVA) will be used to assess changes in various time points, offering evidence at a 95% confidence interval to evaluate the effects on the final clinical result. SDs and outcomes in each time point at the mean change will comprise descriptive statistics and linear regression random-effects models will be used to describe the differences in mean changes between the groups.

As for the underlying missing data or incomplete adherence in this protocol, regardless of normal study attrition, steps to minimize the loss of follow-ups and maximize adherence to the rehabilitation program will be taken. A sensitivity analysis will be conducted to analyze the missing data and their potential effect on the final result, as well as an evaluation of the baseline comparability between the traditional rehabilitation group and the psychological intervention group. Any changes in protocol design will be recorded with reasonable justifications.

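### The abstract names two primary outcomes (mHHS and VAS), section 4.5 names and sizes only one (6-month mHHS change), and the quality-of-life objective matches neither designation

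*Protocol article*

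**What the plan says.** Four places in the protocol article bear on what is primary.

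- **Abstract:** "The primary outcomes will include the modified Harris Hip Score (mHHS) and the Visual Analogic Score (VAS"). This gives two outcomes and no primary time point. ROM, HEI and DASS-21 follow as secondary outcomes, and then: "Furthermore, the Patient Health Questionnaire-9 (PHQ-9) and a Short-Form 12 (SF-12) questionnaire will also be evaluated".
- **Section 4.5 (Sample Size):** "The primary endpoint will be altered from baseline to 6 months post-surgery in the mHHS scale". This gives one endpoint, in the singular, with a time point, an SD (8.7) and a target difference (8 points). VAS does not appear in the section.
- **Section 4.6 (Statistical Analysis):** "Primary outcomes will be estimated to determine the statistical significance (at a significance level of 0.05"). The outcomes are plural but not named.
- **Introduction, last paragraph:** the "primary objective is to compare the effectiveness of different psychosocial therapies for improving the quality of life of FAI participants" with persistent symptoms after surgery.

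Table 1 schedules mHHS, VAS and SF-12 at baseline and at 1, 3 and 6 months, and marks none of them as primary.

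**The concern.** The primary outcome decides whether the trial has succeeded. One section says that two outcomes carry that decision; another says one does. Nothing in the article reconciles them, for example by saying that the trial has two primary outcomes and is sized on the first.

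Two things are at stake. First, a report could present a significant VAS result as a primary finding, citing the abstract, even if the mHHS endpoint failed. VAS was not sized, and two outcomes each tested at 0.05 carry more than a 5% chance of at least one false positive. Section 2.4 says that patients and physiotherapists cannot be blinded, which makes an unplanned claim on a pain score less welcome. Second, the objective is about quality of life, while the sized endpoint is a hip pain and function score. SF-12 measures quality of life but is placed after the secondary outcomes, with no stated rank.

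**Working it through.** **Inputs.** From section 4.5: effect size d = 0.8, power 90%, 34 per group, 15% loss, 40 recruited per group, SD 8.7, MCID 8. From section 4.6: significance level 0.05, with neither sidedness nor a split stated. From the abstract: 200 patients; from section 2.3: five groups of about equal size. Assumed, because the document does not give them: two-sided testing, and a correlation between mHHS and VAS of 0, 0.5 or 0.7.

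**Step 1: reproduce the plan's figure.** A two-sample t-test (noncentral t) with d = 0.8, two-sided alpha 0.05 and power 0.90 needs n = 33.83, so 34 per group; power at 34 is 90.2%. A one-sided 0.05 test would need 28, which does not match. Loss: 34 / (1 − 0.15) = 40. Total: 5 × 40 = 200. The stated size therefore fits one comparison of one outcome at an unsplit 0.05, which is the section 4.5 reading.

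**Step 2: false-positive rate if success on either outcome counts.** For one contrast with independent outcomes, 1 − (1 − 0.05)² = 0.0975. The rest comes from simulation under no effect (34 per group, shared control, two-sided t-tests at 0.05):

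| Assumed correlation | One contrast, either outcome | Four contrasts, mHHS only | Four contrasts, either outcome |
|---|---|---|---|
| 0 | about 10% | about 16% | about 29% |
| 0.5 | about 9% | about 16% | about 27% |
| 0.7 | about 8% | about 16% | about 25% |

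The share due to the second primary outcome is 3 to 5 percentage points for one contrast (8 − 5 to 10 − 5) and about 9 to 13 points over four contrasts (25 − 16 to 29 − 16). The 16% itself comes from comparing four arms with control.

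**Step 3: cost of keeping both outcomes with alpha split.** At two-sided 0.025 and d = 0.8, mHHS power with 34 evaluable falls from 90.2% to 84.0%. Restoring 90% needs n = 40.07, so 41 evaluable; 41 / 0.85 = 48.2, so 49 recruited per group and 5 × 49 = 245 in total.

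**Step 4: cost if both must be significant.** VAS has no SD or target difference, so this can only be illustrated by giving VAS the same standardised effect as mHHS. With d = 0.8 for both and 34 evaluable, joint power is about 81% to 85% (correlation 0 to 0.7). With d = 8 / 8.7 = 0.92 for both, mHHS power alone is 96% and joint power about 92% to 94%.

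**The case against.** A journal article condenses. The analysis rule for two primary outcomes and the primary time point for VAS may stand in a full protocol or SAP that is not shown, and their absence alone would not be a finding. That stands. It is also acceptable to size a trial on one of two primary outcomes. But condensing explains omissions; it does not explain one section naming two primary outcomes and another naming one.

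Four stronger readings are tempting and should not be drawn.

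- A reader might see pain as a further rival primary, because section 4.6 sets out to "discover the connection between the relief of pain or discomfort post-operation and the medical staff’s psychological intervention". But section 4.1 says that mHHS covers pain as well as function, and VAS is in the abstract's pair, so this purpose is compatible with both.
- A reader might infer that VAS has no 6-month measurement. Table 1 schedules one; what the article lacks is a designated primary time point for it.
- A reader might infer that the outcome can be chosen freely once data are seen. Section 4.5 fixes measure, time point and size for mHHS, so the latitude is limited to a possible claim on VAS.
- A reader might infer that requiring both outcomes must bring power below 90%. Step 4 shows that this depends on the assumed effects.

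The quality-of-life point is also a mismatch between objective and endpoint, not a third primary endpoint: the article never calls SF-12 primary.

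**Conclusion.** The inconsistency is real and lies in the current text: two primary outcomes in the abstract, an unnamed plural in section 4.6, one endpoint in section 4.5, and an objective that corresponds to no designated primary outcome. The sample-size arithmetic is not at fault; it supports the single-endpoint reading.

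The size is moderate. For one contrast, the error rate rises from 5% to about 8–10% if success on either outcome counts. Over four contrasts it rises from about 16% to about 25–29%, and a reader might attribute all of that to the two outcomes, but more than half is five-arm multiplicity and would remain. These figures rest on two-sided testing at an unsplit 0.05, 34 evaluable per group and assumed correlations of 0 to 0.7. VAS power cannot be computed from the article. The point should be corrected before outcome data are seen, because it governs what may be claimed.

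**What to change.** **Preferred.** State 6-month mHHS change as the single primary endpoint in the abstract, section 4.5 and section 4.6; it is the only endpoint with a designated time point, an SD and a target difference. List 6-month VAS as a key secondary, tested for a therapy only if that therapy's mHHS contrast is significant. The sample size stays as it is. The cost is that VAS loses co-primary status.

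**Equally valid.** Keep mHHS and VAS as primary in all three places, with 6 months as the time point for VAS and one stated rule:

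- alpha is split, with mHHS power restated as about 84% at d = 0.8 with 34 evaluable (or 41 evaluable and 49 recruited per group to restore 90%); or
- both must be significant, with joint power restated once a VAS target difference and SD are given.

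The cost is a less favourable stated power or more patients.

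**In either case,** align the primary objective in the Introduction with the chosen primary outcome, and list SF-12 as the secondary quality-of-life outcome. Both are wording changes, plus a registry update if the trial is registered. Neither option deals with the four comparisons against control, which need their own rule.

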## 1. Introduction

Femoroacetabular impingement (FAI) is one of the clinical syndromes characterized by femoral head or/and acetabulum anatomic abnormalities that mostly occurs in young adults, especially young athletes, accompanied by symptoms of gait abnormality, groin pain, or mobility limitation. To treat FAI, hip arthroscopy plays an important role in modern hip-preserving surgery, with minimal invasiveness, fast recovery time, and a low rate of complications [1,2]. Furthermore, its postoperative benefits are considerable, including an increased length of stay and decreased pain. The common factors that affect its outcomes include surgical technique, rehabilitation, and the patient’s psychological state. Among these, psychological factors may influence a patient’s postoperative outcomes the most, determining whether they return to sport.

Adverse effects related to psychological factors, including anxiety, pain, and delirium management, together with narcotics-related complications and other postoperative symptoms, may result in more severe conditions, such as morbidity and mortality [3,4]. Although some researchers have verified that pain before surgery occurs more often than post-operation, studies on the postoperative pain and discomfort of angiogenic factors have also been reported, especially at 3, 6, and 12 months after surgery [5,6]. However, on the other hand, an insufficient quantity of research suggests a lack of cases, and no standardized approach to pain management has been summarized.

Improvements in psychosocial factors are strongly related to a participant’s quality of life and activity abilities. Waerden et al. conducted an exercise and a psycho-education program and collected the short- and long-term outcomes. They found that exercise combined with psycho-education may be an option for depression prevention in women with low levels of education [7]. Hu et al. conducted research on floatation therapy in the Chinese population and found that it provided a deepened state of relaxation, reducing stress levels and improving subjects’ emotional states [8].

Additionally, patients after total hip or knee arthroplasties with infection suffered from psychological burdens, implying a correlation [9]. Bay et al. performed a systematic psychological evaluation of total hip arthroplasty (THA) patients and found that psychological interventions were not routinely applied for THA; therefore, determining the applicable conditions for and optimal usage of THA is still required [10]. Additionally, there were no comparisons between different psychosocial interventions in FAI patients in the literature.

Therefore, this trial’s primary objective is to compare the effectiveness of different psychosocial therapies for improving the quality of life of FAI participants with persistent postoperative symptoms. The secondary objective is to determine the relationship between clinical effectiveness, patients’ feedback, and relative cost-effectiveness.

## 2. Materials and Methods

### 2.1. Study Design and Recruitment

A parallel-group randomized controlled trial will be conducted according to the Standard Protocol Items: Recommendations for Interventional Trials (SPIRIT) checklist. Participants will be asked to sign the informed consent document before treatment. Then, we will randomize them into either the intervention or control group before treatment. The educational intervention will be the same in both groups. An examination of patients’ feedback, as well as a relative cost-analysis, will be performed at the last follow-up. Detailed information is presented in Figure 1.

### 2.2. Eligibility Criteria

The inclusion criteria include the following: (1) initially diagnosed with FAI and received treatment by arthroscopy; (2) positive postoperative radiological diagnosis of hip joint rehabilitation; and (3) anxiety and depression symptoms on the HEI scale at pre-operation was ≥8.

The exclusion criteria include the following: (1) patients with severe psychiatric disorders requiring medical treatment or other interventions; (2) revision surgery; and (3) participants who meet the contraindications according to the specific therapeutic intervention program.

Ethics approval was attained from the West China Hospital Ethics Committee; written consent will be provided by each individual.

### 2.3. Randomization and Allocation Concealment

The randomization schedule will be completed by the study biostatistician’s computer-generated random numbers table. The allocation ratio will be generally equal for patients allocated in the five groups mentioned above. Participants and physiotherapists will both receive random numbers sealed in envelopes. The matching envelopes will be allocated and stored by a researcher not participating in any recruitment, treatment, or assessment process.

### 2.4. Blinding

Patients or physiotherapists cannot be blinded during the postoperative treatment of psycho-related content in these specific educational contexts. Conversely, researchers that guide the patients to complete the data will be blinded, as will be the data statistician responsible for analyzing the statistics and data outcomes.

### 2.5. Baseline Data Collection

The genders, ages, occupations, durations of pain or other discomfort, medications, surgical and psychosocial interventions, surgical records, and scanning of images will be recorded.

### 2.6. Intervention

All patients diagnosed with FAI have already undergone hip arthroscopy with debridement or the repair of labral tears, and the postoperative rehabilitation would have been conducted at West China Hospital. Patients in the TAU or traditional rehabilitation group will be applied to a semi-structural rehabilitation program with modified exercise prescriptions according to the individual’s assessment.

Patients will be instructed to perform isometric contractions within one day before the surgery. After two weeks, partial weight bearing with assistive devices, including crutches and braces, will be recommended, together with passive range-of-motion and anterior capsule stretching exercises [7,8]. The hip joint should not be performed external rotation at leass than three weeks postoperatively [9]. Within 4–8 weeks after surgery, the extent of weight bearing will be decided by the patient’s endurance during rehabilitation, with practices, including muscle strength, balance, and cardiorespiratory exercises. In addition, posterior capsule stretches will be conducted gradually. Sports activities will be advised at 6–8 weeks after surgery, with a return to sports achieved after approximately 10 weeks of rehabilitation [9,10].

## 3. Psychological Intervention

### 3.1. Educational Intervention

The participants will receive different psychoeducation programs according to their allocation. All subgroups will receive treatment, including cognitive behavioral therapy and progressive muscle relaxation intervention, during the program [11]. Each session will last for 20–30 min, and the patients will receive a semi-structured dialogue together with brief written advice (BWA) adjusted according to their contemporary situation [12]; furthermore, positive feedback will be provided after each treatment [13]. One session will be conducted per week for six weeks, and the whole evaluation process will last for 3–6 months, with assessments covered in every follow-up. Inpatient therapy will be conducted during patients’ stay at the hospital, while for patients after discharge, therapy will be conducted through at-home training or outpatient sessions [14,15,16]. The purpose of the whole intervention is to achieve emotional relief and self-relaxation.

The educational program will be conducted face-to-face (Group 2) or by telephone (Group 3) according to the participant’s actual condition, including transportation inconveniences. Before the psychological intervention, stretching exercises will be conducted for relaxation in all subgroups [13]. The psychoeducation contents in each group will be much the same, with a semi-structured dialogue given by the nurses or physiotherapists, with necessary guidance and contents, including patient experience sharing, situation sharing that may cause depression and stress, information sharing, problem-solving, skill training, etc. This ensures dialogue completeness, with roughly the same contents and consistency for each group [12,17,18]. In particular, information about pain and sleep management skills; advice on gradual build-up activities, as well as the pace and consistency of activity; and explanations of rest and conditioning will be provided in detail [19,20].

Furthermore, both groups will be efficiently verified based on previous research [21,22], while the discrepancy between group 2 and group 3 would mainly lie in experience sharing, in which team sharing is expected to have a better result due to the potential situational entrapment while communicating and sharing. One expected difference between the reported face-to-face group and the telephone group is that the latter may have difficulties in understanding certain aspects due to the lack of facial and visual cues [17,23].

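### Section 3.1 lets the participant's condition and transport decide between face-to-face (Group 2) and telephone (Group 3), which contradicts the random five-group allocation described elsewhere in the protocol

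*Protocol article*

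**What the plan says.** Four places in the protocol article bear on how a patient comes to be in Group 2 or Group 3.

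- **Abstract:** "The participants will be divided into intervention (telephone versus face-to-face versus music versus floatation) and control groups". Telephone and face-to-face are two of four named intervention arms.
- **Section 2.1:** "Then, we will randomize them into either the intervention or control group before treatment". Only a two-way split is mentioned.
- **Section 2.3:** "The randomization schedule will be completed by the study biostatistician’s computer-generated random numbers table", and "The allocation ratio will be generally equal for patients allocated in the five groups mentioned above". Sealed envelopes are held by a researcher with no part in recruitment, treatment or assessment.
- **Section 3.1:** the opening sentence reads "The participants will receive different psychoeducation programs according to their allocation". The next paragraph says delivery is "face-to-face (Group 2) or by telephone (Group 3) according to the participant’s actual condition, including transportation inconveniences".

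The primary objective in Section 1 is to "compare the effectiveness of different psychosocial therapies for improving the quality of life of FAI participants with persistent postoperative symptoms", so contrasts between individual therapies are central. Section 3.1 also predicts a difference between Groups 2 and 3 and attributes it to group sharing and to visual cues.

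**The concern.** The sentence in Section 3.1 attaches group numbers to the two delivery modes and makes the choice depend on patient characteristics. Read literally, it is a rule for arm membership. One patient's membership of Group 2 or Group 3 cannot be decided both by a random table and by condition and travel difficulty.

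Condition and transport can plausibly relate to function, pain, mood, adherence and attendance. If they decide delivery mode, a later difference between telephone and face-to-face could reflect who was sent where. It would compete with the explanation that Section 3.1 offers for such a difference. The baseline items listed in Section 2.5 include no travel or distance variable, so that part of the selection would be hard to adjust for.

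Groups 2 and 3 hold 80 of the 200 planned patients, and the trial's main question depends on comparing single therapies.

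**Working it through.** **1. The plan's own sample size.** Section 4.5 gives an effect size of 0.8, power of 90% and 34 per group, raised to 40 for 15% loss. Section 4.6 gives a significance level of 0.05. A two-sided two-sample t-test with these inputs needs n = 33.83, so 34 per group. Then 34 / (1 − 0.15) = 40, and 5 × 40 = 200. The figures reproduce, and this point does not touch them.

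**2. The rules side by side.**

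| Place | What decides Group 2 or Group 3 |
|---|---|
| Abstract | Separate arms; mechanism not stated |
| 2.1 | Silent; only intervention or control is mentioned |
| 2.3 | Random numbers table, about equal across five groups |
| 3.1, opening | Allocation |
| 3.1, second paragraph | Participant's condition, including transport |

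No section says that the choice of mode is a recorded departure after randomisation or a stratum. The conflict is therefore unresolved.

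**3. Contrasts affected if the Section 3.1 sentence is followed.** Five arms give 5 × 4 / 2 = 10 pairwise contrasts. Three of them (control, music and flotation among themselves) do not involve Groups 2 or 3, so 10 − 3 = 7 do. One of the seven is Group 2 versus Group 3; the other six set one of these arms against control, music or flotation.

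**4. How the bias spreads.** Suppose the educational patients as a whole are a random sample, a share p goes to telephone, and those patients have a prognosis D worse than the patients kept face-to-face. Relative to the whole population, Group 2 is shifted by +pD and Group 3 by −(1 − p)D.

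- Group 2 versus Group 3: bias D.
- Group 2 versus another arm: pD. Group 3 versus another arm: (1 − p)D in size. With p = 0.5, both are D/2.
- Groups 2+3 pooled versus control: (1 − p) × pD − p × (1 − p)D = 0. This holds only because assignment to education as a whole was taken to be random.

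**5. Illustrative false-positive rates.** Assumptions: no true effect, 34 evaluable patients per arm, p = 0.5 and an unadjusted two-sided t-test at 0.05. For a standardised shift δ, the noncentrality is δ × √(34/2), with 66 degrees of freedom and a critical value of 1.997. For δ = 0.5 the noncentrality is 0.5 × 4.123 = 2.06. The points column uses the protocol's SD of 8.7.

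| Assumed gap D between Groups 2 and 3 | mHHS points | Group 2 vs Group 3 (shift D) | Either arm vs control, music or flotation (shift D/2) |
|---|---|---|---|
| 0.2 SD | 1.7 | 12.8% | 6.9% |
| 0.3 SD | 2.6 | 23.0% | 9.3% |
| 0.5 SD | 4.4 | 52.9% | 17.4% |

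**6. Uneven split.** If 30% went to telephone, the 68 evaluable patients would divide about 48/20 instead of 34/34. With D = 4 points, the rates are about 40% for Group 2 versus Group 3, 9% for Group 2 versus control (bias 0.3 × 4 = 1.2 points) and 20% for Group 3 versus control (bias 0.7 × 4 = 2.8 points).

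**The case against.** The strongest reply is that one loosely worded sentence in a condensed article should not outweigh the rest. Section 2.3 describes a random table, about equal allocation and concealed envelopes. The Abstract names separate arms, Section 4.5 plans 40 per group, and Section 3.1 itself says that programmes follow allocation. The sentence may only explain why a telephone arm is offered, or describe an accommodation after allocation.

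This stands in part. A reader might infer that the five-arm randomisation is overridden and that delivery mode is never randomised. The document does not establish that. It contradicts itself and leaves open which rule governs. The two-way wording in Section 2.1 adds little, since it may be ordinary shorthand for five groups specified elsewhere.

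A reader might also infer that every contrast using Groups 2 or 3 is confounded. That goes too far. A pooled Groups 2+3 versus control contrast would stay randomised if mode were chosen only within a randomised education allocation. Nor do the higher error rates apply to all seven pairwise contrasts: with an even split, six of them carry half the shift.

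Finally, Section 4.6 plans ANCOVA, and Table 1 has mHHS, VAS and the mood scales at baseline. Baseline adjustment could remove part of the bias, but not the part due to unmeasured factors.

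What remains is that no other text neutralises the sentence. It is an affirmative statement about who enters which group, so it is not a detail left to a statistical analysis plan.

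**Conclusion.** The point holds as an internal contradiction. Section 3.1 ties membership of Group 2 or Group 3 to condition and transport. Section 2.3, the Abstract and the opening of Section 3.1 point to random allocation.

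If the sentence is followed, face-to-face versus telephone is a non-randomised comparison, and the six other pairwise contrasts that use one of these arms are biased to a lesser degree. Confidence is high on the contradiction. The documents cannot show which rule will be applied.

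The error rates rest on an assumed prognostic gap, an even split, 34 per arm and no covariate adjustment. Neither the size nor the direction of any real gap can be derived from the documents. Correction is still needed, because analysis could not reliably restore a randomised comparison once patients had been sorted by circumstance.

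**What to change.** Reconcile Sections 2.1, 2.3 and 3.1 in one of two ways.

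**(a) Delivery mode is randomised.**
- Delete the clause in Section 3.1 that refers to condition and transport.
- State in Sections 2.1 and 2.3 that each participant is randomised equally to one of the five named arms, delivery mode included.
- Confirm before randomisation that the participant can accept either delivery mode.
- Analyse anyone who later switches mode in the arm assigned.

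The cost is a wording change and one screening question. The downside is that some patients who cannot travel would not be enrolled; the documents give no figure for how many.

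**(b) Delivery mode is meant to follow circumstances.**
- Declare one randomised education arm with non-randomised mode.
- Do not present Group 2 versus Group 3, or either mode alone versus another arm, as a randomised comparison.

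This keeps patients with travel difficulty in the trial. The cost is the loss of the randomised face-to-face versus telephone question, and the arm structure and the sample size text would have to be revised to match.
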